## LIST OF ABBREVIATIONS AND RELEVANT DEFINITIONS

|                |                                                                                                                                                                                                                                                                                                                                                  |
|----------------|--------------------------------------------------------------------------------------------------------------------------------------------------------------------------------------------------------------------------------------------------------------------------------------------------------------------------------------------------|
| ABR     | ABR form (General Assessment and Registration form) is the application form that is required for submission to the accredited Ethics Committee (ABR = Algemene Beoordeling en Registratie)                                                                                                                                                |
| AE      | Adverse Event                                                                                                                                                                                                                                                                                                                             |
| AR      | Adverse Reaction                                                                                                                                                                                                                                                                                                                          |
| CA      | Competent Authority                                                                                                                                                                                                                                                                                                                       |
| CCMO    | Central Committee on Research Involving Human Subjects                                                                                                                                                                                                                                                                                    |
| CV      | Curriculum Vitae                                                                                                                                                                                                                                                                                                                          |
| DSMB    | Data Safety Monitoring Board                                                                                                                                                                                                                                                                                                              |
| EU      | European Union                                                                                                                                                                                                                                                                                                                            |
| EudraCT | European drug regulatory affairs Clinical Trials GCP Good Clinical Practice                                                                                                                                                                                                                                                               |
| IB      | Investigator's Brochure                                                                                                                                                                                                                                                                                                                   |
| IC      | Informed Consent                                                                                                                                                                                                                                                                                                                          |
| IMP     | Investigational Medicinal Product                                                                                                                                                                                                                                                                                                         |
| IMPD    | Investigational Medicinal Product Dossier                                                                                                                                                                                                                                                                                                 |
| METC    | Medical research ethics committee (MREC); in Dutch: medisch ethische toetsing commissie (METC)                                                                                                                                                                                                                                            |
| (S)AE   | Serious Adverse Event                                                                                                                                                                                                                                                                                                                     |
| SPC     | Summary of Product Characteristics (in Dutch: officiële productinformatie IB1-tekst)                                                                                                                                                                                                                                                      |
| Sponsor | The sponsor is the party that commissions the organisation or performance of the research, for example a pharmaceutical company, academic hospital, scientific organisation or investigator. A party that provides funding for a study but does not commission it is not regarded as the sponsor, but referred to as a subsidising party. |
| SUSAR   | Suspected Unexpected Serious Adverse Reaction                                                                                                                                                                                                                                                                                             |
| Wbp     | Personal Data Protection Act (in Dutch: Wet Bescherming Persoonsgegevens)                                                                                                                                                                                                                                                                 |
| WMO     | Medical Research Involving Human Subjects Act (Wet Medisch-wetenschappelijk Onderzoek met Mensen)                                                                                                                                                                                                                                         |

## SUMMARY

**Rationale:** Age-related macula degeneration (AMD, encompassing both dry and wet form), the late stage of Age-related maculopathy (ARM), is the leading cause of blindness in many developed countries [1-6] in older persons (usually over 60 years of age). Visual compromise rises exponentially after age of 70 [7] with a 5-year incidence of around 1%. Studies have shown a possible protective effect of lutein on progression of AMD, where visual acuity improves after increased lutein intake [8]. The incidence of bilateral AMD in persons with unilateral late ARM observed over a period of 10 years of over 50% with a 2.1-2.8% overall incidence in study population [9].

Blue light hazard (excitation peak 440nm) was shown to have major impact on photoreceptor and RPE function inducing photochemical damage and cellular apoptosis, leading to retinal degeneration in animal study [10]. The current belief is that lutein accumulated in the macular region helps in the prevention of blindness by absorbing blue light and protecting the retina from oxidative stress [11]. With the lipid matrix of the egg yolk being a proven vehicle for the efficient absorption of dietary lutein [12], it might be possible to increase plasma levels of lutein to therapeutic levels and control or prevent AMD. This we hope will be accomplished by means of filtering out harmful blue light and the scavenging of free radicals by lutein and zeaxanthin.

### Objective:

1. Assess any change in macular pigmentation due to lutein and zeaxanthin enriched egg consumption. Our hypothesis is that eggs are very effective at increasing macular pigment optical density by increasing the amount of lutein and zeaxanthin in the *macula lutea*.
2. Assessing changes in retinal morphology, visual acuity and contrast sensitivity. We will also analyze lipid profile in its relation to daily egg consumption.

This study uses some of measuring techniques mentioned in protocol id MEC 06-1-052 where tropicamide is also used and also measures macular pigment optical density.

**Study design:** Randomized placebo controlled interventional trial, where subjects divided into 5 groups, will be consuming either no eggs, normal eggs (lutein:  $0.168 \pm 0.08$ , zeaxanthin  $0.085 \pm 0.0017$ ), eggs enriched with lutein (lutein:  $0.921 \pm 0.106$ , zeaxanthin:  $0.137 \pm 0.014$ ), eggs enriched with zeaxanthin (lutein:  $0.174 \pm 0.014$ , zeaxanthin:  $0.487 \pm 0.031$ ), or egg product made from the lutein enriched eggs. The omega-3 concentration is the same for all eggs and is  $200 \pm 10$ mg. Subjects will pick up their test product (if applicable) at every control session and twice between every control session they will have to come to the Human Biology distribution department to receive additional products. The control group

#### Influence of modified eggs on macular pigment

will be asked to not consume any addition eggs to what they normally do, and everyone will be asked not to make any substantial change to their normal diet.

**Study population:** Healthy human volunteers, 18 years and older.

**Intervention (if applicable):** Each individual will consume one egg or egg product daily for 90 days. The trial group will receive the modified eggs or egg product while the control group will receive conventional egg.

| In egg (mg/egg) | Lutein
Mg per egg yolk |          | Zeaxanthine
Mg per egg yolk |          |
|-----------------|---------------------------|----------|--------------------------------|----------|
|                 | mean                      | St dev   | mean                           | St dev   |
| Control         | 0,16778                   | 0,008655 | 0,08504                        | 0,001692 |
| Lutein          | 0,921422                  | 0,105767 | 0,137318                       | 0,013953 |
| Zeaxanthine     | 0,1743                    | 0,014454 | 0,487303                       | 0,031019 |

#### Main study parameters/endpoints:

- Macular pigment optical density

#### Nature and extent of the burden and risks associated with participation, benefit and group relatedness:

Subjects have to change their diet to the extent that they will have to include one egg or egg product daily to their lunch. Depending on the group they are enrolled in, these eggs or egg products will be made from conventional eggs or modified eggs. Those consuming conventional eggs or egg product will not at any time be exposed to any additional risk compared to their normal egg consumption. There is to date no evidence that indicate that daily egg consumption will increase the risk of cardio vascular disease, as daily egg consumption may result in an increase in cholesterol levels [13, 14]. Those consuming the modified eggs or egg products will be ingesting a higher amount of lutein, zeaxanthin and omega-3 fatty acid than they would otherwise do. These have however been proven safe for consumption at the levels we will be testing [15-17].

The mean visual acuity test using the Early Treatment Diabetic Retinopathy Study (ETDRS)-chart and the contrast sensitivity test using the Pelli Robson chart are also non-invasive. These too will require time and cooperation of the test subject. Further measurements will be performed using various techniques. These have all been used in previous research or clinical settings and proven safe for use on subjects. The Scanning Laser Ophthalmoscope (SLO)[18, 19], Optical Coherence Tomography (OCT, being used daily at our own ophthalmology department), Heterochromatic Fluorescence Photometry (HFP) [20], and the Reflectometer (RM) [21] have all been proven safe. However, all these measurements will take time to be performed and the patient will have to sit still during the whole measuring procedure last approximately 50 minutes per session. All these test will be performed at all three visits.

---

#### **Influence of modified eggs on macular pigment**

---

The same applies to the blood sampling (approximately 10 minutes). This will also be performed 3 times, once every visit. There is the possibility of the occurrence of a haematoma at the insertion site but this is a self-limiting and non life threatening situation. It's extend can, if need be, be further limited by adding extra compression at the site. If and when there is a haematoma, it will be cleaned by the body's own immune system.

The questionnaire will be taken once, at start of the trial, consisting of 15 items.  
A nutrition diary will be kept for three different days during the whole trial.

For some of the measurements the pupil will be dilated using Tropicamide 0.5%, this is also a standard practise at our ophthalmology department with only sporadic, and treatable side effects (acute angle-closure glaucoma in 0.03% of all subject being dilated) [22, 23]. This dilation will be done at every visit.

|                             | Day 1 | Day 45 | Day 90 |
|-----------------------------|--------------|---------------|---------------|
| Visual Acuity test   | X     | X      | X      |
| Contrast sensitivity | X     | X      | X      |
| SLO                  | X     | X      | X      |
| HFP                  | X     | X      | X      |
| OCT                  | X     | X      | X      |
| Reflectometer        | X     | X      | X      |
| Blood Sampling       | X     | X      | X      |
| Questionnaire        | X     | -      | -      |

## 1. INTRODUCTION AND RATIONALE

Age-related macula degeneration (AMD, both wet and dry form) is one of the leading causes of blindness in the elderly (60 years or older) in many parts of the World [24-29]. Recent studies have estimated the current prevalence of AMD from around 1.47% [30] in the United States, where they predict that 2.95 million people will have AMD by 2020, to as high as 3.5% in United Kingdom [9]. There more than half of the registered blindness (54.5%) is due to degeneration at the macula or posterior pole. A cumulative 5-year person specific incidence of 1% was found which climbed to 2.8% after 10-year follow-up. Klein et al found a more conservative 2.1% incidence [31].

AMD is subdivided into two types. The most common form is dry AMD (85%). Secondly there is wet or Choroidal neovascularization (CNV). Because of the variety of pathogenic factors underlying AMD, there is no straightforward treatment for AMD and posing the question whether we are dealing with completely different diseases [32]. Studies to date however find the same genetics behind both forms of AMD [33].

Current treatment methods focus mainly on the CNV form of AMD. Injections with Bevacizumab and Ranibizumab monthly for 2 years resulted in up to 2 lines of visual acuity gain on a standardized eye chart compared to 2 or more lines loss in control groups [34-37]. But these, like other therapies as thermal laser surgery [32] and photodynamic therapy [38], only modulate the disease and have their limitations. Autologous retinal pigment epithelium (RPE) transplantation is one feasible surgery technique but studies still show varying degrees of in results and complications [39, 40]. While this technique also showed positive effect on geographical atrophy AMD, a dry form of AMD, also with the same restrictions as for CNV [41], there still is no established treatment for the dry form of AMD.

Blue light hazard (excitation peak 440nm) was reported to have major impact on photoreceptor and RPE function inducing photochemical damage and cellular apoptosis, leading to retinal degeneration in animal study [10]. The current believe is that lutein and zeaxanthin accumulated in the macular region can help in the prevention of AMD by absorbing this blue light and protecting the retina from oxidative stress by neutralizing free radicals [11, 42-46]. With the lipid matrix of the egg yolk being a proven vehicle for the efficient absorption of dietary lutein [12, 47-49] and zeaxanthin [50], it is be possible to increase plasma levels and macula levels [51]. This may lead to therapeutic levels and be able to control or prevent AMD [11, 43, 45, 52].

#### **Influence of modified eggs on macular pigment**

---

Omega-3 fatty acids have in some studies been shown to prevent AMD [53, 54], when combined with a low omega-6 fatty acid diet [55], but data to date remains inconclusive [56]. The possible protective nature of omega-3 is believed to work by regulating inflammatory and immune response in the retina, repairing damaged cells, and improving endothelial cell function [53].

In this study we hope to show that the consumption of enriched eggs or egg products will lead to an increase in the macular pigment optical density. This we hope can then slow the progression of AMD (both dry and wet) and maybe prevent its onset.

## 2. OBJECTIVES

Primary Objective: Assessing macular pigments' spatial distribution and the changes after consumption of modified eggs compared to normal eggs.

Secondary Objective(s): Assessing changes in retinal morphology, visual acuity and contrast sensitivity. We will also evaluate lipoprotein metabolism in relation to daily egg consumption.

### 3. STUDY DESIGN

This will be a randomized placebo-controlled trial. The total study time will be two years of which 3 months actual trial and follow up time. Every individual will have 3 measuring point at set interval. At every measuring point (days 1, 45 and 90) these subjects will undergo 6 different non-invasive measuring techniques. These are the mean visual acuity test using the Early Treatment Diabetic Retinopathy Study (ETDRS)-chart, contrast sensitivity using the Pelli-Robson chart, Scanning Laser Ophthalmoscope (SLO), Optical Coherence Tomography (OCT) and Heterochromatic Flicker Photometry (HFP) and the Reflectometer. A questionnaire will be taken at the beginning of the trial. The invasive part of the study involves blood sampling at all three times, measuring the serum concentration of lutein, zeaxanthin, omega-3 and lipoprotein using the HPLC analysis.

At the beginning and twice more during the trial period, test subject will keep a nutrition diary for one day.

## 4. STUDY POPULATION

### 4.1 Population (base)

One hundred (100) healthy subjects 18 years and older will be included.

### 4.2 Inclusion criteria

- No history of ARM or AMD
- 18 years and older
- Non-smoker
- No ocular media opacity
- Uses no nutritional supplements containing Lutein, Zeaxanthin or Omega-3
- BMI < 30
- No known cardiovascular disease

### 4.3 Exclusion criteria

- Diabetes
- Other known eye disease
- Known lipid metabolism disease
- Blood lipid level modifiers (e.g. Statin)
- Known allergy to eggs or egg products

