## TREATMENT OF SUBJECTS

### 4.5 Investigational product/treatment

Each individual will consume one egg or egg product daily for a period of 90 days. These will be either modified or control eggs. The expiration time for eggs is 28 days. By using boiled eggs stored in a refrigerator this shelf life can be extended to 8 weeks.

The buttermilk product, which is pasteurized, tested for cooled shelf life for a period of 6 weeks, and 4 weeks at room temperature.

Testing shows the following concentrations for the eggs:

| In egg (mg/egg) | Lutein
Mg per egg yolk |          | Zeaxanthine
Mg per egg yolk |          |
|-----------------|---------------------------|----------|--------------------------------|----------|
|                 | mean                      | St dev   | mean                           | St dev   |
| Control         | 0,16778                   | 0,008655 | 0,08504                        | 0,001692 |
| Lutein          | 0,921422                  | 0,105767 | 0,137318                       | 0,013953 |
| Zeaxanthine     | 0,1743                    | 0,014454 | 0,487303                       | 0,031019 |

The omega-3 concentration is the same for all eggs and is  $200 \pm 10$ mg.

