### **5.6 Dosages, dosage modifications and method of administration**

Test subjects will receive one of four different products to consume during the trial period of 90 days. These will all contain 0.921422 mg/egg (st dev  $\pm$  0.105767) of Lutein, 0.487303 mg/egg (st dev.  $\pm$  0.031019) of Zeaxanthin, and 200 ( $\pm$  10) mg of Omega-3 fatty acids. The dosage is stated as approximately as there are either eggs or egg-products which are produced naturally and as so the concentration will vary from between eggs. The concentration in the egg product will be more uniformly as these are made from a single batch, which will give less variation in concentration than for those subjects consuming the egg itself. These products has to be taken daily for 90 days at lunch time as either an egg or a buttermilk drink containing one egg yolk.

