#### **Influence of modified eggs on macular pigment**

---

The buttermilk drink will be prepared by Coppelmans and packed in 100 ml bottles. The products will be transported to the Human Biology distribution facility where test subjects can collect their products.

Returned products from test subjects will be returned to Newtricious, which will assure the destruction of the remaining products.

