### **6.4 Withdrawal of individual subjects**

Subjects can leave the study at any time for any reason if they wish to do so without any consequences. The investigator can decide to withdraw a subject from the study for urgent medical reasons. Data collected from subject will be destroyed immediately.

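### The exclusion criteria cover allergy to eggs only, although one arm drinks a buttermilk product daily, so a volunteer with known milk allergy or intolerance is eligible and can be allocated to it

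*Protocol*

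**What the plan says.** Section 4.3 lists five exclusions, and one of them concerns the study product: "Known allergy to eggs or egg products". The inclusion list in section 4.2 has no allergy or intolerance item. Neither list mentions milk, dairy or lactose.

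The Summary describes five groups, the last of which receives "or egg product made from the lutein enriched eggs". The product sections show what this is. Section 4.5 speaks of "The buttermilk product, which is pasteurized" and sets the intake for everyone: "Each individual will consume one egg or egg product daily for a period of 90 days". Section 5.6 says that the products are taken "as either an egg or a buttermilk drink containing one egg yolk". Section 5.8 adds that the drink is "packed in 100 ml bottles".

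Section 6.2 assigns subjects to groups by drawing lots, without blinding and with no stated restriction. Section 4.4 sets 20 subjects per group, allowing 10% dropout from a requirement of 18, and section 4.1 gives 100 in total. On withdrawal, section 6.4 says "Data collected from subject will be destroyed immediately". Section 6.5 on replacement is marked not applicable, and section 6.6 provides no follow-up of those who leave.

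**The concern.** The protocol accepts that a person known to be allergic to the test food should not enter, but it applies this to only one of the two named components of the drink. Under allocation by lot, everyone enrolled must be able to take every product, because nobody knows beforehand which one they will get. As written, a volunteer with a known milk allergy passes all criteria and may be handed a milk product to take daily for 90 days. The risk sections do not close the gap. The Summary's burden-and-risk text and section 5.4 discuss egg intake, cholesterol, carotenoids and omega-3, but not milk.

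The first thing at stake is a foreseeable and avoidable exposure. The second is a possible imbalance in retention. Someone who cannot tolerate the drink has a reason to stop that exists in one arm only, and section 6.4 would then remove whatever data that person had already given.

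**Working it through.** **Step 1: the eligibility text against the product text.** No figure in the protocol bears on whether the gap exists, so this step is a comparison of sections.

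- Section 4.3: egg allergy excluded; milk allergy and lactose intolerance not named.
- Section 4.2: no allergy or intolerance item.
- Summary and sections 4.5, 5.6, 5.8: one group of five takes a buttermilk drink, daily, for 90 days.
- Section 6.2: allocation by lot, no restriction by tolerance.
- Section 6.3, Questionnaire: topics include diet and lifestyle; no allergy item is named, and the questionnaire is not described as an eligibility check.

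A milk-allergic, egg-tolerant volunteer therefore satisfies every written criterion. With equal groups, the chance of the buttermilk arm is 20/100 = 1 in 5.

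**Step 2: how many subjects could be affected.** The protocol gives no prevalence of milk allergy or intolerance, so the rate p is an assumption shown over a range. The number affected among 20 is taken as binomial: expected number = 20p; chance of at least one = 1 − (1 − p)^20. The allowance in the arm is 20 − 18 = 2, so three or more would exceed it, but only if every affected subject stops, which is a further assumption.

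| Assumed p | Expected in 20 | Chance of at least one | Chance of three or more |
|---|---|---|---|
| 1% | 0.2 | 18% | 0.1% |
| 2% | 0.4 | 33% | 0.7% |
| 5% | 1 | 64% | 7.5% |
| 10% | 2 | 88% | 32% |
| 20% | 4 | 99% | 79% |

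**Step 3: what a lost subject costs in power.** First, the plan's own figure. The Dutch text of section 4.4 gives a difference of 9%, a measurement error of 7% (used as the SD), a Bonferroni-corrected alpha of 0.017 and beta 0.1. A two-sided two-sample t-test with standardised difference 9/7 = 1.286 and power 0.90 needs 17.8 per group, which rounds up to the stated 18. Then 18/(1 − 0.10) = 20, as stated.

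On the same inputs:

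- 18 against 18: power 0.904
- 17 against 18: power 0.894

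One subject lost beyond the allowance costs 0.904 − 0.894 = 0.010, or about one percentage point. The English comment in section 4.4 quotes a different repeatability (11.7%) and alpha (0.05). That difference is a separate matter, and the power figures here rest on the Dutch inputs.

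**The case against.** Four points can fairly be made against the concern.

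*Volunteers would exclude themselves.* Section 9.2 provides oral information on the trial's implications, three days to decide and room for questions, and section 6.3 requires a signed statement of understanding. The questionnaire also covers diet. The consent pages and questionnaire items are not in the available text, so milk may be named there. This stands in part: it makes exposure less likely, and someone who declines before the lot affects all arms equally. It is still not an eligibility rule.

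*The phrase on egg products already covers the drink.* The protocol does call the buttermilk drink an egg product. The plain meaning of the criterion is egg allergy, though, and lactose intolerance is not an allergy, so it stays uncovered on either reading.

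*The numbers are assumptions.* This stands. The prevalence is not in the protocol, and not everyone who is intolerant would stop because of one drink a day. The last column of the table is an upper end for each assumed rate.

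*The statistical harm is small.* This stands too. A reader might infer that dropout in one arm breaks the randomised comparison of egg product with egg. The protocol does not support that. The primary objective in section 2 compares modified with normal eggs and does not single out the drink against the egg. Nothing in the protocol links milk tolerance to macular pigment or its response, so there is no stated route from selective loss to bias. Nor does section 6.5 forbid replacement; it says only that the heading does not apply. The destruction of data under section 6.4 is a general weakness that affects every arm.

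**Conclusion.** The gap is real on the text. Section 4.3 does not match the products described in 4.5, 5.6 and 5.8, and a volunteer with known milk allergy or intolerance can be enrolled and allocated to the buttermilk arm. It should be corrected, mainly on safety grounds.

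The statistical effect is secondary. Dropout confined to one arm is possible, but its size cannot be fixed from the protocol. The 1-in-5 chance assumes equal groups as planned, the counts assume a prevalence, and the chance of exceeding the allowance also assumes that every affected subject stops. The cost of one further loss is about one percentage point of power on the Dutch sample-size inputs. The point is an unnecessary exposure and an avoidable source of uneven retention. It does not invalidate the comparison between arms.

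**What to change.** Reconcile section 4.3 with 4.5, 5.6 and 5.8 so that the exclusion criteria cover known allergy or intolerance to every component of every study product, including the buttermilk base. Apply them to all subjects before the lot is drawn, so that everyone randomised is eligible for every arm. Screening only those who draw the buttermilk arm would itself create the imbalance. The investigators should settle the clinical wording of the criterion.

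The cost is one criterion and one screening question. A few volunteers would be excluded, and the result would then apply to milk-tolerant adults. The sample size does not change.
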